#### Null hypothesis

There is no difference in TTP in patients with intermediate stage HCC treated with ^90^Y-RE or TACE-DEB.

The alternative hypothesis is two-sided (^90^Y-RE could have a shorter or a longer TTP).

#### Statistical analyses

The primary outcome of the study will be time to progression. Kaplan-Meier analysis will be performed to compare time to progression between treatment arms and difference in TTP will be tested by using the log rank test. The Hazard Ratio (and 95% confidence interval) will be calculated by univariate analyses. A *P-*value of less than .05 will be considered to be statistically significant. Analyses will be performed according to the intention to treat principle. In addition, per protocol analysis will be performed, including only those patients who completed the treatment protocol originally allocated. In terms of secondary outcomes, we will analyze time to local progression and overall survival by means of Kaplan Meier analysis, and test differences between the two arms with log rank test. Differences in proportions of patients reporting toxic/adverse events or treatment related complications will be analyzed by means of a chi square test. Differences in quality of life (as measured by standard questionnaires) over time between the two arms will be analyzed by means of Linear Mixed Model analysis. Statistical analysis of results will be performed with the aid of SPSS software (SPSS Inc., Chicago, Illinois, USA).

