### Study design

This is a pragmatic, multicenter, randomized controlled trial. Patients will be recruited after referral by their hepatologist or another treating physician. Treatment allocation will be performed by minimization, which is a valid alternative to standard randomization to ensure balance between groups for several prognostic factors [30]. The following prognosis-related patient characteristics will be taken into account: Child-Pugh stage (A/B), ECOG performance status (0/1), prior curative (resection or percutaneous ablation) treatment (yes/no) and bilobar disease (yes/no). The minimization procedure will be stratified by treatment center, with the aid of validated software, whereby a random component (10%) is to be introduced.

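### TTP is analysed without the factors used to minimize allocation; if those factors are prognostic, the log-rank test is conservative and loses some power

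*Protocol article*

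**What the plan says.** The Protocol article, Study design, states that "Treatment allocation will be performed by minimization". It introduces the four binary factors with the words "The following prognosis-related patient characteristics will be taken into account": Child-Pugh stage, ECOG performance status, prior curative treatment and bilobar disease. It adds that "The minimization procedure will be stratified by treatment center", "whereby a random component (10%) is to be introduced".

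Statistical analyses says of the primary outcome that "difference in TTP will be tested by using the log rank test", and that "The Hazard Ratio (and 95% confidence interval) will be calculated by univariate analyses". No strata or covariates are named. Time to local progression (TLP) and overall survival are also compared by Kaplan-Meier analysis and a log-rank test; no HR is mentioned for them. The sample size calculation is likewise based on a log-rank test.

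**The concern.** The design treats four characteristics and centre as important enough to balance, and the analysis then leaves them out. Minimization removes much of the chance variation between arms in those factors. The variance of an ordinary log-rank test still allows for that variation. If the factors influence the outcome, the test statistic varies less than its reference distribution assumes. P-values are then too large on average, confidence intervals too wide, and power is lost. The same applies to TLP and overall survival. Since the word univariate is written into the plan, this is a choice made in the text and not a detail left for elsewhere.

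**Working it through.** **The plan's own figure.** Sample size calculation gives 70 per arm for 90% power, two-sided 5%, median TTP 13.3 months after 90Y-RE, a 2.7-month difference and 24 months of follow-up. Reading this as 13.3 against 10.6 months with exponential times:
- HR = 10.6/13.3 = 0.797.
- Events = 70 × (1 − 2^(−24/13.3)) + 70 × (1 − 2^(−24/10.6)) = 70 × 0.714 + 70 × 0.792 ≈ 105.
- Power = Φ(½√105.4 × |ln 0.797| − 1.96) = Φ(1.165 − 1.96) ≈ 21%.

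The stated 90% is not reproduced. With 105 events, 90% power needs HR = exp(−2 × (1.960 + 1.282)/√105) = 0.53. This is a separate problem. It is shown here because it supplies two treatment effects for the comparison: 0.797 (as planned) and 0.53 (where 140 patients give about 90% power).

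**Prognostic strength in the document.** The Background section on 90Y-RE gives median TTP by Child-Pugh class for intermediate-stage patients: 13.3 months (A) and 17.4 months (B). Under exponential times the HR for B against A is 13.3/17.4 = 0.76. Nothing comparable is given for the other three factors or for centre.

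**Simulation.** 6,000 trials per scenario, N = 140, minimization on the four factors within centre, exponential TTP censored at 24 months. Assumptions: 10% of allocations made purely at random, three centres, factor prevalences of 25, 35, 30 and 50%, the factor HRs shown, and centre HR spreads of 1.0 (first two rows), 1.2 (next two) and 1.5 (last). Unadjusted is the log-rank test. Adjusted is a Cox score test with the four factors, stratified by centre. Entries are percentages, unadjusted / adjusted.

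| Factor HRs | Type I error | Power, HR 0.797 | Power, HR 0.53 |
|---|---|---|---|
| All 1.0 | 5.4 / 6.1 | 21.4 / 21.9 | 92.2 / 91.8 |
| Child-Pugh 0.76, others 1.2 | 5.2 / 6.0 | 19.5 / 21.2 | 91.1 / 91.4 |
| Child-Pugh 0.76, others 1.5 | 4.0 / 5.5 | 17.5 / 21.4 | 88.6 / 91.6 |
| All 1.5 | 3.9 / 6.1 | 17.5 / 20.7 | 88.2 / 91.6 |
| All 2.0 | 2.8 / 5.7 | 12.5 / 21.1 | 78.7 / 90.1 |

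The Monte Carlo standard error of the unadjusted type I error is 0.2 to 0.3 points. With two or six centres and all factor HRs at 1.5, unadjusted type I error is still 3.9%.

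**Mechanism.** The standard deviation of the log-rank Z under the null is 0.957 with all HRs at 1.5 and 0.905 with all at 2.0. The size is roughly 2Φ(−1.96/SD), which gives 2Φ(−2.05) ≈ 4.1% and 2Φ(−2.17) ≈ 3.0%, in line with the simulated 3.9% and 2.8%. With all HRs at 2.0 but simple randomization, the standard deviation is 0.999 and the size 5.0%. The conservatism therefore comes from ignoring the minimization.

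**Second run.** A separate simulation (2,000 trials per scenario, three centres, treatment HR 0.55) agrees in direction. With factor HRs near 1.5, type I error is about 3.9% and power 79 to 81% unadjusted against 82 to 84% adjusted. With HRs of 2.0, power is 70% against 83%. Near 1.2 there is almost no difference.

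**The case against.** - **The size rests on assumptions.** This stands. The document gives a TTP figure for one factor only, from a 90Y-RE series, and calling the factors prognosis-related does not say that they predict radiological progression. With weak factors the unadjusted plan loses next to nothing.
- **The comparison flatters adjustment.** Partly true. The adjusted score test runs at 5.0 to 6.1%, and a Wald test at about 5.5 to 6.5%, so some of the power gap is excess size. It is unlikely to be all of it: with no prognostic effect the adjusted test has a similar size (6.1%), yet gains 0.5 points at HR 0.797 and nothing at HR 0.53.
- **The plan is valid and cautious.** True. A reader might infer that the primary test is unsafe, but the error runs towards missing a difference and not towards a false claim.
- **The univariate HR is legitimate.** True. A reader might infer that it is biased towards 1. The adjusted HR lies further from 1 mainly because hazard ratios are non-collapsible: the marginal and the conditional HR answer different questions, and a trial described as pragmatic may want the marginal one.
- **A fuller plan may add an adjusted analysis.** Possible, and the article does not exclude a supportive one. It does commit the HR for TTP to a univariate analysis.

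**Conclusion.** The mismatch between allocation and analysis is stated in the text. Its direction is well supported; its size is conditional.
- Factor HRs near 1.5: type I error of about 3.9 to 4.0% at a nominal 5%, and about 3 to 4 power points lost.
- All factor HRs at 2.0: type I error of 2.8%, and about 9 points lost at HR 0.797 or 11 at HR 0.53 (about 13 at HR 0.55 in the smaller run).
- Factor HRs near 1.2: negligible.

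These figures depend on the assumed prevalences, factor HRs, number of centres and reading of the random component. A reader might also infer that adjustment would rescue the trial's power. It would not: at the planned difference power is about 21% even with adjustment. This is a modest efficiency loss that is worth correcting because the correction is cheap.

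**What to change.** Prespecify as the primary TTP analysis a Cox model with treatment and the four minimization factors as covariates, stratified by centre, with small centres pooled by a rule set in advance. Test the treatment effect by a score or likelihood-ratio test. Use the same model for TLP and overall survival. Keep the unadjusted log-rank test and Kaplan-Meier curves as supportive, and align the test named in Sample size calculation.

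No new data are needed, because the factors are recorded at allocation. Trial status reports 10 patients minimized and results pending, so at that point the change could be fixed before outcomes were seen.

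The costs are that the primary HR becomes conditional on the factors and must be reported as such, and that the test may run slightly above 5% at about 105 events. The sample size calculation has to be corrected separately.

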### Intervention

#### TACE

TACE will be performed with drug-eluting beads, that is, polyvinyl alcohol-based microspheres (DC Bead®, Biocompatibles, Farnham, UK), 100 to 300 μm in diameter, loaded with the chemotherapeutic agent doxorubicin. Patients will receive a maximum dose of 150 mg doxorubicin per single treatment session. No dose adjustment will be made for bilirubin concentration or body surface area. Dose determination is based on previous dose escalation studies, in which DEBs loaded with doxorubicin up to 150 mg were shown to be safe and effective [19,20], and recommendations from the literature [17,22]. After mixing with nonionic contrast medium, the DEBs will be slowly injected under fluoroscopic visualization while the contrast flow rate is observed; the embolization endpoint will be reached when all the DEBs are administered (maximum dose is reached), or earlier when sluggish flow is seen (to avoid reflux and non-target embolization). Total administered dose will be recorded.

Injection of DEBs will be performed as selectively as possible after Cone-Beam CT confirmed perfusion of the target lesions. If selective administration is not possible, a lobar treatment will be performed. The TACE procedure will be repeated after two months. A third TACE at four months after initial treatment will only be performed in the case of residual enhancement on the three months follow-up contrast-enhanced MRI scan of the liver. The moment of the first treatment will be defined as trial entry.

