#### ^90^Y-RE

^90^Y-RE will be performed using glass Yttrium-90 microspheres (TheraSphere®, MDS Nordion, Ottawa, Ontario, Canada). The target dose to the liver will be 100 to 120 Gy. The procedure will be carried out over two separate sessions: a work-up session and a treatment session. Meticulous work-up is very important because it determines the overall safety of the treatment. First, a selective visceral catheterization will be performed in order to obtain an angiographic map of the patients’ vascular anatomy. Branches feeding gastro-intestinal organs arising from the hepatic arteries must be identified. Radioactive microspheres, administered into the hepatic artery, should be prevented from ending up in extrahepatic organs via this route. The interventional radiologist will actively look for the presence of the gastroduodenal artery, right gastric artery, cystic artery and pancreaticoduodenal branches. If required, these arteries will be embolized using coils, taking the planned catheter position for injecting the microspheres into account. Additionally, 150 MBq Technetium-99 m-labeled macro aggregated albumin (^99m^Tc-MAA) will be injected. ^99m^Tc-MAA is used as a surrogate in order to predict the distribution pattern of ^90^Y-microspheres [31]. The distribution of ^99m^Tc-MAA will be visualized by whole body planar imaging and single-photon emission computed tomography (SPECT-CT), including low dose computer tomography of the abdomen. Accordingly, lung shunt fraction can be calculated and deposition of ^99m^Tc-MAA in the abdominal organs, such as the stomach, duodenum and pancreas, can indicate patent extrahepatic vessels distal to the injection site. In case a lung dose exceeding 30 Gy (610 MBq) in a single treatment (or 50 Gy cumulatively in case of repeated treatment) is predicted, an activity reduction will be prescribed [32].

In case a patient has an unfavorable ^99m^Tc scintigraphy, the ^99m^Tc-MAA workup procedure will be repeated, if feasible, to detect the cause of the extrahepatic deposition (for example, previously undetected patent extrahepatic vessels arising from the hepatic artery) and a solution will be searched for (for example, more selective placement of the catheter during injection). In the unlikely event no solution can be found and ^90^Y-RE cannot be performed, the patient will be treated according to best medical practice and will still enter the intention-to-treat analysis in the ^90^Y-RE arm.

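### Harms have only an intention-to-treat set and a completers-only set: add a toxicity comparison by treatment actually received

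*Protocol article*

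**What the plan says.** The Statistical analyses section gives one general rule, "Analyses will be performed according to the intention to treat principle", placed after the log-rank test and hazard ratio for time to progression (TTP) and before the secondary outcomes. It then adds a second set: "per protocol analysis will be performed, including only those patients who completed the treatment protocol originally allocated". For harms it says: "Differences in proportions of patients reporting toxic/adverse events or treatment related complications will be analyzed by means of a chi square test". That sentence names no analysis set, and the article mentions no safety or as-treated population.

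The 90Y-RE section applies the general rule to one case. When 90Y-RE cannot be performed after work-up, "the patient will be treated according to best medical practice and will still enter the intention-to-treat analysis in the ^90^Y-RE arm". It introduces that case with the words "In the unlikely event no solution can be found" and gives no rate.

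Three other places matter. The Follow-up section monitors adverse events for six months after the last treatment procedure and does not tie this to the allocated procedure. The treatment sections plan repeat sessions: for TACE, "The TACE procedure will be repeated after two months", and for bilobar disease 90Y-RE is given one lobe at a time. The Objective section names efficacy and safety together.

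**The concern.** Intention to treat suits TTP and survival. For harms it answers one question, what follows from allocation to a strategy, and leaves another open: what harm does each procedure do to those who receive it? Readers of a comparison of two procedures will want both answers.

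The two arms are not alike here. Only 90Y-RE has a planned step between allocation and treatment that can fail. The article calls TACE the current standard for these patients, so TACE is a plausible substitute, although the text says only that best medical practice will apply. Complications of a substitute TACE would fall in the 90Y-RE column.

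The per-protocol set cannot fill the gap. A patient who stops after one of two planned sessions because of toxicity has not completed the protocol and leaves that set, so membership depends on the outcome being measured.

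At stake is how clearly the trial can show a difference in toxicity with 70 patients per arm. The Study rationale section itself cites a retrospective comparison that found less toxicity with radioembolization.

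**Working it through.** The plan states no figure on this point, so there is none to reproduce. The check has two parts, both illustrative.

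**Inputs from the article:** 70 patients per arm (Sample size calculation); post-embolization syndrome in 37% to 100% of patients treated with TACE (Background). **Assumed, because not given:** the share *f* of the 90Y-RE arm that receives TACE after failed work-up, the 90Y-RE toxicity rate *pR*, an overall TACE toxicity rate *pT*, and the share *s* of patients with toxicity who stop early.

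**1. Intention to treat.** The rate in the 90Y-RE arm is (1 − f)·pR + f·pT, so the shift is f·(pT − pR).

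With pR = 20% and pT from 37% to 100%:

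| f | patients (70 × f) | shift, percentage points |
|---|---|---|
| 2% | 1.4 | 0.02 × 17 = 0.3 to 0.02 × 80 = 1.6 |
| 5% | 3.5 | 0.05 × 17 = 0.85 to 0.05 × 80 = 4.0 |
| 10% | 7 | 0.10 × 17 = 1.7 to 0.10 × 80 = 8.0 |

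With pR = 20% and pT = 40%, and power for a two-sided 5% test of two proportions:

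| f | 90Y-RE rate by intention to treat | difference from TACE | power, intention to treat | power, by treatment received |
|---|---|---|---|---|
| 0% | 20.0% | 20.0 points | 0.74 | 0.74 |
| 2% | 20.4% | 19.6 points | 0.72 | 0.73 |
| 5% | 21.0% | 19.0 points | 0.69 | 0.73 |
| 10% | 22.0% | 18.0 points | 0.64 | 0.71 |
| 15% | 23.0% | 17.0 points | 0.58 | 0.70 |

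The last column removes the failed work-up patients from 90Y-RE and does not add them to TACE.

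The direction is not fixed. If those patients received no procedure and had no events, 5% of them would lower a 20% rate to 0.95 × 20% = 19.0%. That is a lower bound, because work-up can itself cause events.

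**2. Per protocol.** If a share s of patients with toxicity stop and everyone else completes, the observed rate is p(1 − s)/(1 − p·s).

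| true rate p | s = 10% | s = 25% | s = 50% |
|---|---|---|---|
| 40% | 0.36/0.96 = 37.5% | 0.30/0.90 = 33.3% | 0.20/0.80 = 25.0% |
| 20% | 0.18/0.98 = 18.4% | 0.15/0.95 = 15.8% | 0.10/0.90 = 11.1% |

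Under these assumptions, the per-protocol distortion can exceed the intention-to-treat one.

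**The case against.** Four points count against this.

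First, the article never says in so many words that toxicity is analysed by intention to treat. The rule stands before the secondary outcomes, and the chi-square sentence names no set. A reader might take it that the plan expressly puts toxicity under intention to treat; that is an inference. A condensed article may also leave a safety set to a full protocol or analysis plan that is not shown. This limits the point but does not remove it: the rule is unqualified, and the 90Y-RE section spells out its consequence for failed work-up.

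Second, the trial is described as pragmatic, and comparing the harms of allocated strategies is a legitimate question. A work-up that can fail is part of the 90Y-RE strategy. A reader might infer that intention to treat is an error for harms; the document does not support that. The objection stands in full, so the intention-to-treat toxicity table should stay.

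Third, failed work-up is expected to be rare and follows a repeat work-up where feasible. The Trial status section reports that all of the first 10 patients adhered to the protocol. The upper figure of 8 points needs 10% failure, TACE for every such patient, and a 100% event rate; the 37% to 100% range covers post-embolization syndrome alone.

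Fourth, the per-protocol analysis is offered as an addition and is not presented as the safety analysis. That is fair: the criticism is only that it cannot serve as one.

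**Conclusion.** The point holds as a modest improvement. On the plain reading, neither stated set shows toxicity by the treatment actually given, and safety is half of the objective. The likely effect of misplaced harms is small. With assumed rates of 20% and 40%, it is 0.4 to 1.0 point at 2% to 5% failure; over the wider TACE range it is 0.3 to 1.6 points at 2%. All of this rests on assumed rates and on TACE being the substitute, which the article does not say.

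A reader might go further and suppose that a patient with failed work-up who gets no procedure counts as event-free under 90Y-RE. The text does not support that. Such a patient has already had visceral catheterization, a 99mTc-MAA injection and perhaps coil embolization, and nothing says that events from these are discarded. Nor do the documents support a claim of large bias.

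**What to change.** Keep intention to treat for TTP, time to local progression, survival and quality of life, and keep the intention-to-treat toxicity table as the comparison of strategies. Then state that:

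- toxicities and complications will also be compared in all patients who started any study procedure, work-up included, by the treatment actually received;
- each patient counts once. Splitting one patient's events between the two columns would break the independence that the chi-square test needs. Patients who received neither procedure are listed separately;
- procedures given after progression do not count, since the plan lets patients change treatment then;
- harms of the work-up are reported separately, as part of the 90Y-RE strategy;
- the per-protocol set is not used for harms.

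The cost is a short paragraph and one more table from data already being recorded. The trial is still recruiting, so the set can be fixed before results are known. The downside is that the added comparison is not fully randomised: patients with failed work-up are a selected group. It should therefore be read beside the intention-to-treat table, not in place of it.

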## Trial status

The trial is currently including patients. The first 10 patients have been minimized and treated according to the allocated treatment arm. Until the present all patients adhered to the trial protocol. First results are pending.

## Ethical approval

The study protocol has been approved by the ethical boards of the participating hospitals.

## Abbreviations

^90^Y-RE: Yttrium-90 radioembolization; ^99m^Tc-MAA: Technetium-99 m-labeled macro aggregated albumin; ALT: alanine aminotransferase; AST: aspartate aminotrasferase; BCLC: Barcelona Clinic Liver Cancer; CT: computed tomography; CTCAE: National Cancer Institute Common Terminology Criteria for Adverse Events; DEB: drug eluting bead; ECOG: Eastern Cooperative Oncology Group; HCC: hepatocellular carcinoma; MRI: Magnetic Resonance Imaging; RECIST: Response Evaluation Criteria in Solid Tumors; SPECT: single-photon emission computed tomography; TACE: transarterial chemoembolization; TTP: time to progression; ULN: upper limit of normal.
